## **11. ETHICAL CONSIDERATIONS FOR PROJECTS INVOLVING HUMAN SUBJECTS**

Research clearance for the proposed study has been obtained from the Medical Research Co-ordinating Committee of the National Institute for Medical Research, which acts as the National Ethics Committee in Tanzania and is attached.

At the beginning of the study meetings will be organized with parents and teachers of the earmarked schools, whereby detailed information will be provided by the research team about the aims, procedures, benefits and potential risks of the study.

Written informed consent will be obtained from all participants. In case of minors, the oral assent of the child will be asked, besides the written consent of the guardian. If the children is between 10-<14, and according to the Investigator's perception, he/she is not able to understand the information given during the informed consent procedure, the oral assent is not necessary.

Participation in the study will be on voluntary terms and that an individual will be free to withdraw from the study at any time. Withdrawal from the study will not affect ones statutory rights in any way.

All records of study subjects will be kept confidential.

All schoolchildren participating in the study and found to have schistosomiasis will be treated free of charge. Participants with schistosomiasis who do not fulfil the criteria for enrolment will be treated with the standard regimen of single dose Praziquantel at 40 mg/Kg.

Only parasitological specimens (Kato-Katz slides) will be kept for the duration of the study to allow for quality control and cross-checking. They will then be discarded. No other specimens will be kept.

## **12. CRITICAL ASSESSMENT AND POSSIBLE LIMITATION OF APPROACH IN RELATION TO PROJECT OBJECTIVES**

12.1. Missing of a single schistosome egg during microscopy in light infections may cause bias in determination of cure rate and egg reduction rate (efficacy) of the investigational product. To minimise bias only subjects with high egg count are included in the trial (see inclusion criteria)

12.2. Praziquantel does not affect immature stages of schistosomes. In order to avoid eggs from immature stages that are not affected by PZQ at the time of treatment, the end point in determination of efficacy is optimised at day 21.

## APPENDIX 1

### Baseline Screening, Treatment and Safety Assessment Schedule:

| Calendar | Day  | No. of subjects Screened | No. Kato Slides Made | Urine samples screened | Stool microscopy | Computer Data entry | D0  | D1  | D21 |
|----------|------|--------------------------|----------------------|------------------------|------------------|---------------------|-----|-----|-----|
| 1        | Mon  | 100                      | 200                  | 100                    |                  |                     |     |     |     |
| 2        | Tue  |                          | 200                  | 100                    | 200              |                     |     |     |     |
| 3        | Wed  | 100                      | 200                  | 100                    | 200              | Xx                  |     |     |     |
| 4        | Thur |                          | 200                  | 100                    | 200              | Xx                  |     |     |     |
| 5        | Fri  | 100                      | 200                  | 100                    | 200              | Xx                  |     |     |     |
| 6        | Sat  |                          |                      |                        |                  |                     |     |     |     |
| 7        | Sun  |                          |                      |                        |                  |                     |     |     |     |
| 8        | Mon  |                          | 200                  | 100                    | 200              | xx                  | X1  |     |     |
| 9        | Tue  | 100                      | 200                  | 100                    | 200              | xx                  |     | X1  |     |
| 10       | Wed  |                          | 200                  | 100                    | 200              | xx                  | X3  |     |     |
| 11       | Thur | 100                      | 200                  | 100                    | 200              | xx                  |     | X3  |     |
| 12       | Fri  |                          | 200                  | 100                    | 200              | xx                  | X5  |     |     |
| 13       | Sat  |                          |                      |                        |                  |                     |     | X5  |     |
| 14       | Sun  |                          |                      |                        |                  |                     |     |     |     |
| 15       | Mon  | 100                      | 200                  | 100                    | 200              | xx                  | X9  |     |     |
| 16       | Tue  |                          | 200                  | 100                    | 200              | xx                  |     | X9  |     |
| 17       | Wed  | 100                      | 200                  | 100                    | 200              | xx                  | X11 |     |     |
| 18       | Thur |                          | 200                  | 100                    | 200              | xx                  |     | X11 |     |
| 19       | Fri  | 100                      | 200                  | 100                    | 200              | xx                  |     |     |     |
| 20       | Sat  |                          |                      |                        |                  |                     |     |     |     |
| 21       | Sun  |                          |                      |                        |                  |                     |     |     |     |
| 22       | Mon  |                          | 200                  | 100                    | 200              | xx                  | X15 |     |     |
| 23       | Tue  |                          |                      |                        | 200              | xx                  |     | X15 |     |
| 24       | Wed  |                          |                      |                        |                  | xx                  | X17 |     |     |
| 25       | Thur |                          |                      |                        |                  |                     |     | X17 |     |
| 26       | Fri  |                          |                      |                        |                  |                     |     |     |     |
| 27       | Sat  |                          |                      |                        |                  |                     |     |     |     |
| 28       | Sun  |                          |                      |                        |                  |                     |     |     |     |
| 29       | Mon  |                          |                      |                        |                  |                     | X19 |     |     |
| 30       | Tue  |                          |                      |                        |                  |                     |     | X19 |     |
| 31       | Wed  | 30                       | X1                   |                        |                  | xx                  |     |     | X1  |
| 32       | Thur |                          | X1                   |                        | X1               | xx                  |     |     |     |
| 33       | Fri  | 30                       | X3                   |                        | X1               | xx                  |     |     | X3  |
| 34       | Sat  |                          | X3                   |                        | X3               | xx                  |     |     |     |
| 35       | Sun  |                          |                      |                        |                  |                     |     |     |     |
| 36       | Mon  | 30                       | X5                   |                        | X3               | xx                  |     |     | X5  |
| 37       | Tue  |                          | X5                   |                        | X5               | xx                  |     |     |     |
| 38       | Wed  | 30                       | X9                   |                        | X5               | xx                  |     |     | X9  |
| 39       | Thur |                          | X9                   |                        | X9               | xx                  |     |     |     |
| 40       | Fri  | 30                       | X11                  |                        | X9               | xx                  |     |     | X11 |
| 41       | Sat  |                          | X11                  |                        | X11              | xx                  |     |     |     |
| 42       | Sun  |                          |                      |                        |                  |                     |     |     |     |

|    |      |    |     |  |     |    |  |  |     |
|----|------|----|-----|--|-----|----|--|--|-----|
| 43 | Mon  | 30 | X15 |  | X11 | xx |  |  | X15 |
| 44 | Tue  |    | X15 |  | X15 | xx |  |  |     |
| 45 | Wed  | 30 | X17 |  | X15 | xx |  |  | X17 |
| 46 | Thur |    | X17 |  | X17 | xx |  |  |     |
| 47 | Fri  |    |     |  | X17 |    |  |  |     |
| 48 | Sat  |    |     |  |     |    |  |  |     |
| 49 | Sun  |    |     |  |     | xx |  |  |     |
| 50 | Mon  | 30 | X19 |  |     | xx |  |  | X19 |
| 51 | Tue  |    | X19 |  | X19 | xx |  |  |     |
| 52 | Wed  |    |     |  | X19 | xx |  |  |     |
| 53 | Thur |    |     |  |     | xx |  |  |     |

Key: X1, X3 etc. refers to the day in which schoolchildren were first screened for schistosomiasis e.g., X1 screened on day 1 of the study calendar.

## APPENDIX 2.

Table 1. Number of praziquantel tablets to be given to subjects under the 40mg/kg and 60mg/kg regimens.

| 40 mg/kg regimen |                   | 60 mg/kg regimen |                   |
|------------------|-------------------|------------------|-------------------|
| Bodyweight (kg)  | Number of tablets | Bodyweight (kg)  | Number of tablets |
| 13-15            | 1                 | 10               | 1                 |
| 16-18            | 1 ¼               | 10 - 12.5        | 1 ¼               |
| 19 – 22          | 1 ½               | 12.6 - 15        | 1 ½               |
| 23 – 25          | 1 ¾               | 15 - 17.5        | 1 ¾               |
| 26 – 29          | 2                 | 17.6 - 20        | 2                 |
| 30 – 33          | 2 ¼               | 20 - 22.5        | 2 ¼               |
| 34 – 37          | 2 ½               | 22.6 - 25        | 2 ½               |
| 38 – 40          | 2 ¾               | 25 - 27.5        | 2 ¾               |
| 41 – 44          | 3                 | 27.6 - 30        | 3                 |
| 45 – 48          | 3 ¼               | 30 - 32.5        | 3 ¼               |
| 49 – 52          | 3 ½               | 32.6 - 35        | 3 ½               |
| 53 – 55          | 3 ¾               | 35 - 37.5        | 3 ¾               |
| 56 – 59          | 4                 | 37.6 - 40        | 4                 |
| 60 – 63          | 4 ¼               | 40 - 42.5        | 4 ¼               |
| 64 – 66          | 4 ½               | 42.6 - 45        | 4 ½               |
| 67 – 70          | 4 ¾               | 45 - 47.5        | 4 ¾               |
| 71 – 75          | 5                 | 47.6 - 50        | 5                 |
|                  |                   | 50 - 52.5        | 5 ¼               |
|                  |                   | 52.6 - 55        | 5 ½               |
|                  |                   | 55 - 57.5        | 5 ¾               |
|                  |                   | 57.6 - 60        | 6                 |

In this table, 13-15 means 13.1 kg to 15.9 kg. The same applies to the other weight ranges

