### 3.3. Randomization:

Schoolchildren with *S. mansoni* and fulfilling both inclusion and exclusion criteria will be randomly assigned to two groups: one group will receive PZQ 40mg/kg and the other group PZQ 60mg/kg. Randomization will be generated in blocks of 4, in a ratio of 1:1 for each drug regimen. Sealed and numbered envelopes containing the treatment regimen for each sequential participant to be enrolled will be provided from TDR. The envelopes containing the codes will be kept in a locked cabinet and one designated person of the team will be responsible for them. This same person will be responsible for opening the envelope and verifying the corresponding treatment once a new participant is enrolled in the study. Each participant will be assigned a unique Study I.D. number (ID#). This ID# will be assigned in sequential order and will be recorded in the Screening Log. The treatment will be provided to the participant according to the Praziquantel regimen assigned by the randomization code and the participant's weight (Appendix 6). An electronic, password-protected copy of the randomization codes will be kept at TDR, Geneva.

The opened envelopes will be signed, dated, resealed and kept in the locked cabinet.

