### 3.4. Blinding:

Blinding of the study will be achieved by ensuring that the person who calculates the dosage of PZQ to be given and provides the medication to the participants is not the person who evaluates safety. In addition those doing the parasitological analysis will not know the treatment given to the individual children.

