#### 4.1. Inclusion criteria

- Age 10-19 years
- Infected subjects with an egg excretion of  $\geq 100$  eggs per gram of faeces for *S. mansoni*.
- Those able and willing to be followed up
- Who have given written informed consent for stool, urine and blood samples. In case of adolescents (< 18 years), written informed consent from their parents and their verbal assent to be obtained.

Those who have satisfied the inclusion criteria will be further tested for the following exclusion criteria:

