### **5. TREATMENT OF SUBJECTS:**

Those schoolchildren who fulfilled inclusion criteria will be recruited for the trial. A total of 236 schoolchildren (see sample size calculation on section 10.2) with *S. mansoni* who fulfilled the inclusion/exclusion criteria would be randomly assigned to two groups of 118 each. One group will be given a single dose of PZQ 40 mg/kg and the other a single dose of PZQ 60mg/kg body weight. Table 2 below illustrates the treatment groups.

Table 2. Study groups for and *S. mansoni* treatment.

| Dosage of PZQ/kg body weight | S. mansoni subjects (N) |
|------------------------------|--------------------------------|
| 40 (single dose) – Control   | 118                            |
| 60 (single dose)             | 118                            |

Praziquantel is provided in tablets of 600mg with 3 scores, which may be divided in 4 segments of 150 mg each. The amount of drug to be given can be adjusted to the patient's bodyweight by breaking the tablets in 4 segments. A reference table for the number of tablets to be given for each participant according to treatment regimen and body weight is presented in Appendix 2.

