#### 6.2.5. Weight

Weight of schoolchildren will be measured at baseline, at 6-months and 12 –months post treatment with PZQ. A digital, battery operated, electronic balance (Tanita digital Model THD - 305) will be used to weigh schoolchildren.

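### PZQ is ordered for infected children excluded for a known PZQ reaction, with no exception; separately and minor, the Appendix 2 footnote fits only one of the two dosing columns

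*Protocol*

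**What the plan says.** **Children excluded for a PZQ reaction.** Section 4.2 lists a known earlier adverse reaction to PZQ as an exclusion. The D0 text in section 3.2 has a questionnaire ask for that history, followed by a physician's examination. The same D0 text then gives a single 40 mg/kg dose of PZQ to infected children excluded at that step. The design text of section 3.2 and section 11 give the same order for infected children who do not meet the entry criteria. Section 4.2 also promises treatment to infected children who are not included, but that sentence does not name the drug.

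**The dosing table.** Section 5 gives one group 40 mg/kg and "the other a single dose of PZQ 60mg/kg body weight". Tablets are 600 mg, "which may be divided in 4 segments of 150 mg each". Section 5 refers to Appendix 2 as "A reference table for the number of tablets to be given for each participant". There, the 40 mg/kg column uses whole-kilogram ranges that do not touch (13-15, 16-18, ... 71-75). The 60 mg/kg column uses half-kilogram ranges, every second pair of which shares a limit (12.6-15 then 15-17.5; 27.6-30 then 30-32.5), and it ends at 60 kg. One footnote governs both: "In this table, 13-15 means 13.1 kg to 15.9 kg. The same applies to the other weight ranges". Section 3.3 sends the reader elsewhere for the same table: "weight (Appendix 6".

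**The concern.** On the first point, the history that keeps a child out of the trial does not affect the treatment the child then receives. Read literally, a child who reports an earlier reaction on D0 is excluded for it and then given the same drug. What is at stake is re-exposure of a non-randomised child without anyone first judging how serious the earlier reaction was.

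On the second point, dose is the only planned difference between the arms, and this table sets tablet counts. If its ranges overlap or leave gaps, two careful dispensers can give different counts at one weight, or find no row.

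**Working it through.** **Safety point.** No arithmetic applies; the texts are set side by side.

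- Section 4.2: a known PZQ reaction excludes.
- Section 3.2, D0: the reaction history is sought, so such a child can be identified at that visit.
- Section 3.2, D0, same paragraph: infected children excluded at that step receive PZQ 40 mg/kg.
- Section 3.2, design text, and section 11: the same order for infected children who fail the entry criteria.
- Section 8.2: children given PZQ are observed for at least 4 hours. This may cover non-randomised children too, but it comes after dosing.

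No section makes an exception or requires the earlier reaction to be reviewed first.

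**Table point.** Inputs:

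- Dose in mg/kg = tablets x 600 / weight; the smallest step is 150 mg (section 5).
- Range limits and footnote from Appendix 2. Literally, a range a-b means a + 0.1 to b + 0.9 kg.
- Assumption: weights in 0.1 kg steps, suggested by the table's own decimals and by the balance (section 6.2.5: "A digital, battery operated, electronic balance"). The recording precision is not stated.
- Assumption: 25 to 60 kg is plausible for "Age 10-19 years" (section 4.1). That is (60 - 25)/0.1 + 1 = 351 weights. The protocol gives no weight distribution.

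Weights, out of 351, without exactly one row:

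| Reading | Two 60 mg/kg rows | No 40 mg/kg row |
|---|---|---|
| Footnote ignored | 7 (2%) | 90 (26%) |
| Footnote literal, all ranges | 119 (34%) | 10 (3%) |
| Lower limit included, upper + 0.9, all ranges | 133 (38%) | 0 |
| Footnote for 40 mg/kg; 60 mg/kg to 0.1 kg, shared limit in the lower row | 0 | 10 (3%) |
| As the row above, but 40 mg/kg lower limits included | 0 | 0 |

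The first three rows each apply one rule to the whole table, and none works. The last row works, but it needs a separate rule for each column, which the footnote does not give. The 10 weights without a 40 mg/kg row are 26, 30, 34, 38, 41, 45, 49, 53, 56 and 60 kg. Over the whole column there are 16 such internal lower limits, plus the 13.0 kg floor.

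Size at single weights:

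- 25 kg, as printed: 1500/25 = 60 or 1650/25 = 66 mg/kg.
- 30 kg, as printed: 1800/30 = 60 or 1950/30 = 65 mg/kg.
- 55 kg, as printed: 3300/55 = 60 or 3450/55 = 62.7 mg/kg.
- 30.7 kg, footnote literal: 1800/30.7 = 58.6 or 1950/30.7 = 63.5 mg/kg.

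Mean 60 mg/kg dose with weights spread evenly over 25 to 60 kg, always taking the lower against always the higher row:

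- Footnote ignored: 61.81 against 61.89, a shift of 0.08.
- Footnote ignored, weights in whole kilograms: 61.46 against 62.24, a shift of 0.78.
- Footnote literal: 60.44 against 61.74, a shift of 1.30.
- Lower limit included, upper + 0.9: 60.44 against 61.89, a shift of 1.45.

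With one unambiguous row per weight, the means are 61.8 and 41.8 mg/kg, so the contrast is 61.8 - 41.8 = 20.0. The largest shift is 1.45/20.0, about 7% of it.

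**The case against.** **On the table.** A sensible dispenser would find the row.

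- Every 60 mg/kg upper limit equals 10 kg per tablet, so 30 kg is 3 tablets and exactly 60 mg/kg.
- The range 26-29 names 26 kg, so a start of 13.1 rather than 13.0 looks like a slip.
- The footnote's example is a whole-kilogram range. Adding 0.9 kg to limits already printed to 0.1 kg is unnatural.
- The highest dose from a printed tie in the assumed range, 66 mg/kg, is below the 75 mg/kg that section 1 describes as well tolerated.

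All of this stands, and it makes the table point minor. What it does not remove is that staff must set aside a written rule to reach the right row.

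A reader might infer that 26% or 34% of children have no dose or two doses. The documents do not support that. The 26% ignores a footnote written to close those gaps, and the 34% needs the unnatural reading. Both count weights, not children. Nor does the stop at 60 kg leave heavier children undosable: section 3.4 refers to "the person who calculates the dosage of PZQ to be given", and the mg/kg dose is fixed in section 5.

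**On safety.** A trial exclusion is not automatically a contraindication to standard care. The term adverse reaction is not defined in section 4.2, and section 1 calls PZQ side effects usually mild. A physician examines children on D0, and section 8.2 provides observation and a resuscitation kit. This is a good reason not to forbid treatment, and the fix does not. But observation after dosing cannot replace review before it, and nothing tells the physician to weigh the earlier reaction. A reader might also infer that section 4.2 itself orders PZQ for these children; its sentence promises treatment without naming the drug. The orders are in sections 3.2 and 11.

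**Conclusion.** Both points hold and should be kept apart.

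The safety point is the one that should be fixed. Sections 3.2 and 11 order PZQ for infected excluded children, including those excluded because of a known reaction to it. It concerns non-randomised children, and its frequency cannot be estimated from the protocol. It rests on the text alone.

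The table point is a minor wording error. The footnote cannot serve both columns. The effect is one quarter tablet at the weights concerned, and about 0.1 to 1.5 mg/kg in the mean 60 mg/kg dose under the assumed weights. A reader might infer that the comparison between arms is compromised; a contrast of about 20 mg/kg does not support that, and sample size and analysis are unaffected. The missing rows above 60 kg are an omission, and the reference to Appendix 6 is clerical.

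**What to change.** **Safety.** Add to the treatment orders in section 3.2 (design text and D0 text) and section 11: *except children excluded for a known PZQ reaction, who are treated only after a study physician has reviewed that reaction.* Cross-refer to this in section 4.2.

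**Table.** Print the 60 mg/kg bands without shared limits: 10.0 kg, 1 tablet; 10.1-12.5, 1 1/4; 12.6-15.0, 1 1/2; 15.1-17.5, 1 3/4; and so on to 57.6-60.0, 6. Replace the footnote with: *In the 40 mg/kg column, 13-15 means 13.0 kg to 15.9 kg, and likewise for its other ranges; the 60 mg/kg ranges are exact to 0.1 kg.* Every weight from 13.0 to 60.0 kg then has exactly one count in each column.

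**Housekeeping.** Extend the 60 mg/kg column by the same rule (quarter tablets = 0.4 x kg, rounded up; for example 60.1-62.5 kg, 6 1/4), subject to clinical approval. Correct the appendix number in section 3.3 to 2.

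The cost is one exception clause with its cross-reference, one reprinted column, one footnote and one appendix number. A physician already examines children on D0, so no visit is added, and design, sample size and analysis do not change.
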